# Comparison of the effectiveness of a tailored cognitive behavioural therapy with a supportive listening intervention for depression in those newly diagnosed with multiple sclerosis (the ACTION-MS trial): protocol of an assessor-blinded, active comparator, randomised controlled trial

**DOI:** 10.1186/s13063-019-4018-8

**Published:** 2020-01-20

**Keywords:** Depression, Cognitive behavioural therapy (CBT), Multiple sclerosis, Newly diagnosed, Randomised controlled trial, Anxiety

## Abstract

**Background:**

Multiple sclerosis (MS) is an unpredictable, chronic neurological disease accompanied with high rates of depression and anxiety, particularly in the early stages of diagnosis. There is evidence to suggest that cognitive behavioural therapy (CBT) is effective for the treatment of depression amongst individuals with MS; however, there is a paucity of tailored CBT interventions designed to be offered in the newly diagnosed period. This trial is the first to assess the effectiveness and cost-effectiveness of a tailored CBT intervention compared to a supportive listening (SL) intervention amongst individuals with MS who are depressed.

**Methods:**

ACTION-MS is a two-arm parallel group, assessor-blinded, active comparator, randomised controlled trial which will test whether a tailored CBT-based intervention compared to an SL intervention can reduce depression and related factors such as anxiety, fatigue, pain and sleep problems in those newly diagnosed with MS. Sixty participants who are within 5 years of having received a diagnosis of MS and scored within the mild to moderate range of depression on the Beck Depression Inventory (BDI-II) will be recruited from MS clinics located across three hospital sites in Melbourne, Australia. The primary outcome is depression severity using the BDI-II at post-assessment. Intervention satisfaction and acceptability will be assessed. A cost-effectiveness analysis will also be conducted. Data will be analysed on an intention-to-treat basis.

**Discussion:**

There is a scarcity of psychological interventions for depression targeting the newly diagnosed period. However, interventions during this time point have the potential to have a major impact on the mental and physical wellbeing of those newly diagnosed with MS. The current trial will provide data on the effectiveness of a tailored CBT intervention for the treatment of depression in those newly diagnosed with MS. Findings will also provide effect size estimates that can be used to power a later-stage multi-centre trial of treatment efficacy, and will provide information on the mechanisms underlying any treatment effects and cost-effectiveness data for delivering this intervention in outpatient MS clinics.

**Trial registration:**

ISRCTN trials registry, ISRCTN63987586. Current controlled trials. Retrospectively registered on 20 October 2017.

## Background

High levels of depression and anxiety have been found around the time of multiple sclerosis (MS) diagnosis [1, 2] with up to 36% of individuals with MS reporting high rates of depression and anxiety in the first 2 years of diagnosis [2–4]. Point prevalence rates of depression range from 10 to 42%, with up to 50% of individuals with MS experiencing depression in their lifetime [5, 6], which is higher than the value for any other neurological condition or chronic illness [7, 8]. Risk factors for depression amongst individuals with MS include functional status, anxiety, fatigue, cognitive impairment, pain [5, 9], losses in physical and cognitive function, occupational roles and social support [9], a reduction in previously pursued activities [10] and disease characteristics including MS illness duration, symptom severity, neurological disability and disease status [7, 11]. Demyelination and inflammation in certain parts of the brain and associated neurological changes have also been found to play a role in the development of depressive symptoms [5]. Depression in individuals with MS has been associated with poor psycho-social and treatment outcomes such as anxiety, fatigue, pain, sleep disturbances, poorer quality of life [2, 12–14], restricted social and economic opportunities [15], reduced medication adherence [16] and MS symptom exacerbations [17].

There is mounting evidence for the effectiveness of cognitive behavioural therapy (CBT) in treating depression amongst individuals with MS. In a recent systematic review and meta-analysis looking at interventions of depression in individuals with MS, Fiest and colleagues [18] identified eight randomised controlled trials that employed CBT-based interventions for the treatment of depression in those with MS and found that the severity of depression scores improved in all trials (standardised mean difference [SMD] – 0.45; 95% confidence interval [CI] − 0.74, − 0.16). Despite these promising findings, research in the treatment of depression amongst individuals with MS has been limited in its methodology, with a paucity of interventions targeted towards individuals who are newly diagnosed. Early psychological intervention is important, considering rates of depression and anxiety have been found to be at clinically high levels around the time of diagnosis [1–4]. Furthermore, if depression is left untreated, it will worsen and contribute to further deterioration, having an impact on the course of MS [19], resulting in exacerbation of relapses [17], higher suicide rates [20] and lower treatment adherence [21]. Early provision of CBT may increase psychological wellbeing, lead to improvements in treatment thereby altering MS disease progression and also lead to better social and functional outcomes for individuals with MS [2].

Tailored CBT approaches adapted specifically for individuals with MS have been found to be more effective and preferred over generic CBT interventions. MS participants have found generic CBT interventions less relevant to their needs [2]. A pilot study by [name] and colleagues [2] found that a tailored early CBT intervention compared to treatment as usual was effective for treating depressive symptoms amongst patients who were within 5 years of being diagnosed with MS. Large between-group treatment effects were found for level of depression at both post-intervention (*d* = 1.66) and 20 weeks follow-up (*d* = 1.34). Those in the tailored CBT intervention also reported significantly greater improvements in quality of life, fatigue and pain management, coping, and sleep quality and reductions in anxiety with medium to large effect sizes at post-intervention and at 20 weeks follow-up (*d* = 1.06–0.44).

### Rationale for the present study

Critique of previous research examining CBT for treatment of depression in those with MS includes lack of active comparator arms, small sample sizes, assessors and therapists not being blinded to participant allocation and a lack of research focused on newly diagnosed individuals [2, 22]. We have developed a tailored CBT intervention for depression and other MS-related concerns including anxiety, fatigue, pain and sleep disturbance for mild and moderately depressed individuals with MS who are within 5 years of being diagnosed. The current study will be a randomised controlled trial comparing the tailored CBT intervention with supportive listening (SL). This will allow us to assess whether there are any particular benefits associated with the tailored CBT intervention compared to SL.

### Objectives

The *primary aim* of this study is to assess the efficacy of a tailored early CBT intervention in treating depression (primary outcome) in individuals who have been newly diagnosed with MS and are experiencing mild to moderate depression. *Secondary aims* of the study are to examine whether those that undertake the CBT intervention will also display significant and clinically meaningful reductions in levels of anxiety. *Tertiary aims* of the study are to examine whether those that undertake the early tailored CBT intervention will also display significantly and clinically meaningful reductions in fatigue and pain impact, and significant improvements in sleep quality, MS-related quality of life, active coping styles, level of MS diagnosis acceptance, resilience and social support. *Quarternary aims* of the study are to examine the cost-effectiveness of the CBT intervention, taking into account benefits to patients, health service usage and cost of interventions.

### Hypotheses

Our *primary hypothesis* is that there will be a significantly higher percentage of participants who achieve a clinically meaningful change of 10 points or more on the Beck Depression Inventory-II (BDI-II) [23] between baseline and post in the CBT intervention compared to those receiving the SL intervention. Our *secondary hypotheses* are that those in the CBT intervention will display a significantly greater change in the BDI-II total score at 20 weeks follow-up compared to those in the SL intervention; and that there will be a significantly higher percentage of participants who achieve a clinically meaningful change of 10 points or more on the State Trait Anxiety Inventory (STAI) [24] between baseline and post in the CBT intervention compared to those receiving the SL intervention. Our *tertiary hypotheses* are that those in the CBT intervention will display a significantly greater change in the STAI total score at 20 weeks follow-up compared to those in the SL intervention; and that those in the CBT intervention will display significant reductions in fatigue and pain impact and significant improvements in level of MS illness acceptance, MS-related quality of life, sleep quality, active coping strategies and resilience at post-intervention (8 weeks) and at 20 weeks follow-up.

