#### Secondary outcome measures

Secondary outcomes are the magnitude of change between baseline and 20 weeks on the BDI-II in the CBT intervention with the level of depression measured with the BDI-II and the magnitude of change between baseline and post-intervention on the STAI. Level of anxiety will be measured with the STAI.

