#### Tertiary outcome measures

Tertiary outcomes are the magnitude of change between baseline and post-intervention on fatigue and pain impact, MS-related quality of life, sleep quality, MS diagnosis acceptance, active coping styles, resilience and perceived social support in the early CBT intervention. Fatigue impact will be measured with the Modified Fatigue Impact Scale-5 item version (MFIS-5) [31]. Pain impact will be measured using the 6-item Pain Effects Scale [31]. Sleep quality will be measured with the Pittsburgh Sleep Quality Index [32]. MS-related quality of life is measured using the 54-item MS-related quality of life measure [33]. Coping styles will be examined using the 66-item Ways of Coping questionnaire [34]. Acceptance of MS illness will be measured using the 10-item Acceptance of Chronic Health Conditions Scale [35]. Level of resilience will be measured with the 33-item Resilience Scale for Adults [36], and Perceived Social Support will be measured using the 12-item Scale of Perceived Social Support [37].

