### Planned statistical analysis

#### Effectiveness analysis

The primary outcome analysis will be an intention-to-treat between-group comparison of the proportion of patients who achieve a clinical and meaningful change of 10 points or more on the BDI-II between baseline and post-intervention adjusted for baseline depression severity using a logistic regression model. Baseline characteristics will be presented by randomised group without formal statistical tests. Secondary and tertiary outcome analyses will be undertaken using appropriate regression models adjusted for baseline depression severity. Longitudinal changes will be examined using regression models. No formal interim analyses for either efficacy or safety are planned, but safety outcomes will be continuously monitored.

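### The secondary anxiety endpoint is a responder percentage in the hypotheses but a magnitude of change in the outcome list, and the tertiary measures and time points do not match either

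*Protocol article*

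**What the plan says.** **Anxiety, baseline to post-intervention.** The secondary hypothesis is a between-arm comparison of percentages: a "significantly higher percentage of participants who achieve a clinically meaningful change of 10 points or more on the State Trait Anxiety Inventory". The list under Secondary outcome measures gives "the magnitude of change between baseline and post-intervention on the STAI". The instrument, interval and tier are the same, but the variable is not. The Objectives section speaks of "significant and clinically meaningful reductions in levels of anxiety", which fits either.

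**Anxiety at 20 weeks.** The tertiary hypotheses include "a significantly greater change in the STAI total score at 20 weeks follow-up". Neither Secondary outcome measures nor Tertiary outcome measures lists it.

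**Tertiary measures.** Hypotheses places them at two times, ending with "active coping strategies and resilience at post-intervention (8 weeks) and at 20 weeks follow-up". The outcome list has one: "Tertiary outcomes are the magnitude of change between baseline and post-intervention on fatigue and pain impact", followed by the remaining measures. Perceived social support appears in Objectives, in the description of the tailored CBT and in Tertiary outcome measures, but not in Hypotheses.

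**Analysis.** Effectiveness analysis says: "Secondary and tertiary outcome analyses will be undertaken using appropriate regression models adjusted for baseline depression severity". It names neither the model type nor the time point for these outcomes.

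**The concern.** A percentage crossing a 10-point threshold and a magnitude of change are different estimands. The first leads to a logistic model and an odds ratio or risk difference, the second to a linear model and a mean difference. They can give different answers in the same data, and they have different power. Anxiety is the whole of the stated secondary aim, so this is the main result after depression.

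With two published definitions, either could be reported as the prespecified one after the data are seen, and a reader could not tell which was intended. The same applies, more mildly, to the number and timing of the tertiary tests. A later analysis plan could choose one version, but it would then contradict a section of the published protocol. The text itself therefore needs correcting.

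**Working it through.** **1. Sections side by side**

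| Item | Hypotheses | Outcome lists |
|---|---|---|
| STAI, baseline to post | percentage with a change of 10 or more | magnitude of change, no threshold |
| STAI, 20 weeks | tertiary hypothesis (total score) | not listed |
| Tertiary measures | 7, at 8 and 20 weeks | 8, at post-intervention only |
| Perceived social support | absent | listed |

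Is magnitude of change merely loose wording for the responder form? The article's own usage says not. Primary outcome measure uses a percentage for the BDI-II responder endpoint. Secondary outcome measures uses magnitude of change for BDI-II at 20 weeks, and there Hypotheses speaks of change in the total score. So magnitude of change denotes the continuous form.

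**2. Number of tertiary tests, read literally**

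- Tertiary outcome measures: fatigue, pain, quality of life, sleep, acceptance, coping, resilience and social support, at one time = 8.
- Hypotheses: the first seven of these at two times, plus STAI at 20 weeks = 7 × 2 + 1 = 15.

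The chance of at least one false positive at 5% each, if independent, is 1 − 0.95^k:

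- k = 8: 1 − 0.663 = 0.337, about 34%.
- k = 15: 1 − 0.463 = 0.537, about 54%.

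Independence is not realistic for self-reported scales in the same patients, or for one scale at 8 and 20 weeks, so these figures are upper illustrations.

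**3. Does the choice of STAI definition matter?**

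The article gives no STAI figures, so all inputs here except the 30 per arm are assumptions: normally distributed change scores, SD 8, 10 or 12, mean change in the supportive listening arm 2 or 5 points, standardised difference d of 0.5, 0.65 or 0.8, and two-sided 0.05.

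- Mean change: power = Φ(d·√(30/2) − 1.96). For d = 0.65: 0.65 × 3.873 = 2.517, and Φ(0.557) = 0.71.
- Responder: P(change ≥ 10) = 1 − Φ((10 − mean)/SD). For SD 10 and a supportive listening mean of 5, the CBT mean is 5 + 0.65 × 10 = 11.5. The rates are 30.9% and 56.0%, and two-proportion power is 0.50.

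Over the whole grid, power is 49% to 87% for mean change and 28% to 68% for the responder form. In matched scenarios the gap is about 16 to 28 percentage points.

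**4. Is the plan's own sample size touched?**

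Sample size calculation states 30 per arm, 90% power, alpha 0.05 and a 45-point difference in the BDI-II responder proportion. With the two-sided pooled formula and no continuity correction, n = [1.96·√(2p̄q̄) + 1.2816·√(p₁q₁ + p₂q₂)]² / 0.45². In the worst case, 27.5% versus 72.5%, this is (1.386 + 0.809)² / 0.2025 = 23.8, so 24 per arm. Allowing an assumed 20% drop-out, 24/0.80 = 30. The control and drop-out rates are not stated, so the figure cannot be reproduced exactly, but 30 per arm is compatible with it. No STAI or tertiary input enters.

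**The case against.** The best reply is that this concerns secondary and tertiary outcomes only. The trial is powered for the primary outcome alone, and its BDI-II responder definition agrees across Hypotheses, Primary outcome measure, Sample size calculation and Effectiveness analysis. The Abstract and Discussion also say that the results will supply effect sizes for a later multi-centre trial, so little confirmatory weight falls on the tertiary tests. This stands, and it limits how serious the point is.

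The reply is also fair on tertiary timing. Assessments sets baseline, 8-week and 20-week visits for both arms, and Effectiveness analysis adds regression models for longitudinal change. The outcome list can therefore be read as naming the main time point and leaving 20 weeks to the longitudinal analysis. On that reading this part is an incomplete listing more than a contradiction. The reading does not rescue the STAI definition, where the interval is the same and the variable differs.

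Two further inferences are tempting and are not supported:

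- A reader might infer that a 10-point STAI fall is out of reach for many participants, because eligibility requires depression and not anxiety. The article gives no baseline STAI distribution, and its Background reports high rates of anxiety around diagnosis.
- A reader might count seven tertiary measures at one or two times, 7 against 14 tests. Neither section gives that count: the outcome list has eight measures, and Hypotheses adds STAI at 20 weeks.

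Finally, the article requires one consistent definition but does not dictate which. The preference for the continuous form is a statistical judgement, and the secondary aim is compatible with the responder form too.

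**Conclusion.** The point holds and should be fixed. The secondary anxiety endpoint has two incompatible definitions, and nothing else in the article settles which is tested. The hypotheses and outcome lists also disagree on STAI at 20 weeks, on tertiary time points and on social support; of these, the time-point difference is the mildest.

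The contradiction itself rests on the text and needs no assumption. Its size is illustrative: 8 or 15 tertiary tests (about 34% or 54% under independence), and a difference of roughly 16 to 28 points of power between the STAI versions under assumed inputs.

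A reader might go further and infer that the primary result or the sample size is in doubt, or that a favourable version has been or will be chosen. The article supports neither. The operative sections agree on the primary endpoint, the sample size does not depend on the STAI, and an open choice is not evidence of selection.

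**What to change.** Amend the wording before unblinding:

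- Use one STAI endpoint identically in Hypotheses, Secondary outcome measures and Effectiveness analysis. The preferred form is the between-arm difference in STAI score at 8 weeks from a linear model adjusted for baseline STAI, in addition to the baseline depression severity already specified. It keeps more information than a threshold. Report the 10-point percentage as supportive.
- Make the measures and time points identical in Hypotheses and the outcome lists, including STAI at 20 weeks and perceived social support. Name post-intervention as the main time point and 20 weeks as follow-up.

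The cost is a text amendment. The sample size does not change, and no visit is added, since both time points are already planned. The schedule figure cannot be read here, so the sponsor should confirm that social support is collected at 20 weeks. The one small loss is that the STAI responder comparison is no longer the formal test.

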## Methods/design

This protocol is reported according to guidelines presented in the Consolidated Standards of Reporting Trials (CONSORT) 2010 statement for clinical trial protocols [25]. Figure 1 displays the CONSORT flow chart of participants through the trial. The Standard Protocol Items: Recommendations for Interventional Trials (SPIRIT) checklist is provided as Additional file 1.

**Fig. 1 Fig1:**
[figure not shown]
CONSORT flow chart of participants through the ACTION-MS trial

### Trial design

The ACTION-MS trial is a prospective, parallel group, assessor-blinded, active comparator, stratified, clinical trial with balanced randomisation (i.e. 1: 1).

### Participant recruitment

Participants will be recruited from MS clinics located at the Royal Melbourne Hospital (RMH), St Vincent’s Hospital and Western Health, Victoria, Australia. Treating neurologists, nurse co-ordinators and a researcher located at these clinics will screen patients with MS who are within 5 years of having received a diagnosis using a screening questionnaire asking two questions (Have you been feeling low most days for the last 2 weeks? and Have you lost interest or pleasure in most things?). If patients positively endorse at least one of these questions and they consent to being contacted, their contact details will be given to the trial manager for further assessment. The trial will be advertised through hospital and MS-related websites, and individuals can also self-refer to the study. The trial manager will review and confirm eligibility of participants. Individuals will be invited to an appointment for a baseline assessment at the RMH site. A total sample of 60 individuals newly diagnosed with MS will be enrolled to take part in the current study based on our pilot trial data [2].

### Consenting participants

Individuals will provide informed consent to participate when they attend the baseline assessment with a clinical psychologist or registrar. No study-specific procedures will take place before written consent has been obtained. After the baseline assessment, the clinical trial manager will confirm eligibility with the participant.

### Inclusion and exclusion criteria

Eligible participants will be a group of mild to moderately depressed patients (i.e. those who have scored between 14 and 28 on the BDI-II) who have been diagnosed with MS by a neurologist within the last 5 years. Exclusion criteria include (1) gross cognitive impairment that would make participation in the eight 1-h sessions of CBT distressing. Cognitive impairment will be assessed with the Brief International Cognitive Assessment for MS (BICAMS) [26]; (2) inability to speak or read English; (3) acute organic brain syndrome (e.g. delirium); (4) serious psychological disorder (e.g. psychosis); (5) those assessed with the BDI-II (a score of 28 or more) and the Structured Clinical Interview for DSM-5 Research Version (SCID-5-RV) [27] as being severely depressed; and (6) currently undertaking psychological treatment for depression and/or anxiety. Those who are taking anti-depressant medication will be accepted after being on the medication for 2 months or longer. Any changes to disease-modifying medication will be recorded.

